**b. Setting**

Location of study procedures and/or data collection: Recruitment will occur in Fulton County Jail. Delivery of the first part of the intervention will be in this jail; the remaining steps will occur in the community, such as in the waiting rooms of HIV clinic offices or other locations convenient for the participants. The study staff will take care that confidentiality of health information will be maintained.

**c. Recruitment: site, procedure, methods**

Jail healthcare staff can approach HIV positive inmates and ask if they would like to have study staff members talk to them about a potential project. If so, they will have potential participants sign a release of information form that will permit them to convey the name of the inmate to study staff. Jail healthcare staff will have a dedicated phone number to make participant referrals to the study staff. A member of the study staff will go to the jail to evaluate the potential participant for eligibility for participation in the study, explain the program, and obtain written informed consent to participate in the study and to release medical records from the jail and from future sites of HIV care. The study staff member will determine if the potential participant has a cell phone on the outside and inform him/her that study incentives will preferentially be paid in cell phone minutes.

All potential participants, regardless of whether they consent to participate in the study, will be given information about where to obtain HIV healthcare near where they plan to settle after release, such as a HRSA/ Ryan White supported clinic. Any written information on how to obtain benefits, medications, and substance abuse care will be written at a sixth grade reading level.

- Plans to monitor equitable recruitment of subjects: N/A for this demonstration project

**d. Study Procedures**

- Study design is a longitudinal cohort study of individuals receiving a behavioral intervention. We will obtain baseline data (demographical data, data extracted from jail medical chart review); deliver an intervention designed to improve linkage to medical care; and then extract data from medical records in the community.
- The research material will be responses to self-report questionnaires, and abstracted data from participants’ medical charts. Records maintained at Emory University will be kept electronically on a strong password protected computer in a locked room. Each record will be assigned a unique code that is, in and of itself, non-identifying. The link to the code will be on a separate sheet of paper without reference to HIV, and will be kept separately in a folder protected by a password known only to the PI and the project coordinator.
- Access to medical records of participants will be limited to those staff responsible for performing chart abstractions. Data from chart abstractions will be stored at Emory and will be identified only by a unique code.
- Procedures for subjects
  - Data collection procedures: the case manager will administer a baseline demographic survey using pen and paper. If the participant has difficulties with reading, the case manager will read the questions to the subject.
  - Other study related interactions:

The **SUCCESS** intervention that has been adapted for the target population is based on ARTAS (see above.). The four core elements of *ARTAS* (1. developing working relationship with client, 2. identifying client’s goals, 3. encouraging client’s strengths, 4. meeting in the client’s environment) will be the core elements of **SUCCESS**.[^65^](#_ENREF_65) Together, a CM and client will navigate through a fragmented and potentially confusing system of diverse resources and agencies. The philosophy of SBCM is to have clients set goals because, while the ultimate goal of **SUCCESS** is to link HIV+ persons to medical care, the subjects

**
[figure not shown]
**initially may not share this goal. The *ARTAS* intervention showed that, through engagement with CMs, clients were drawn to greater participation in medical care.[^7^](#_ENREF_7) The **SUCCESS** intervention will follow the objectives and strategies of the *ARTAS* manual distributed by the CDC,[^66^](#_ENREF_66) with 3 adaptations: 6 rather than 5 *ARTAS*-like SBCM sessions, the use of mobile phones and texting, and the use of low literacy audio-visual aids in the sessions. The **SUCCESS** intervention will be delivered by the study’s three CMs, with the first 2 sessions (or “contacts”) designed to occur in jail, pre-release. Release dates in a jail can be unpredictable. If a study participant is released prior to completion of the first 2 contacts, those contacts will occur in the community. Subsequent contacts are designed to occur in the community post release, but they can take place in jail if release is delayed. **Session 1** will begin with development of a “contact plan”, a systematic and structured plan to help a participant access medical services. A CM will spend approximately 1.5 to 2 hours face-to-face with a participant for the provision of three initial services: 1) Completion of forms so that HIV drug benefits can be initiated/continued including AIDS Drug Assistance Program (ADAP) or indigent drug assistance programs, insurance and Medicaid forms, and forms to obtain a non-correctional picture ID and a birth certificate; 2) Making referrals to local substance abuse treatment programs if drug or alcohol dependency is an issue for a participant and to mental health care if the mental health screen was positive; and 3) Confirming a participant’s choice of a clinic where high quality, specialty HIV care can be obtained, tailored to a participant’s needs or preferences (e.g. the choice between a neighborhood clinic to facilitate access versus a clinic across town to facilitate privacy). A discussion of how to arrange transportation and engage in services after jail discharge will also be held. A participant can always choose later to change medical homes. Rapport building and a personal strength assessment will take place at **Session 2** which will be ideally scheduled before or on the day of release. A key element of the intervention is the social support that will be offered to a participant to help him or her cope with illness and other stressful situations including having his or her CM meet a detainee at the jail’s exit door, since such meetings have been associated with improved linkage outcomes..[^57^](#_ENREF_57)^,^[^67^](#_ENREF_67) At the end of Session 2, a participant and his or her CM will decide where to meet upon release.

Figure 2. Client Flow in **SUCCESS**

Post-release sessions will ideally take place in the medical clinic (such as the Ponce Center or the AID Atlanta medical clinic) but can occur at another, mutually agreed upon, safe, public location, such as a coffee shop; public transportation to the meetings will be reimbursed. **Session 3** will occur around the time of a participant’s release from jail, preferably on the day of release. It will focus on reviewing how to make contact with the medical clinic if no medical visit has yet occurred. In addition, a CM will confirm that a participant has access to a cell phone. Many releasees will have personal cell phones available to them; we will provide basic cell phones for those without mobile phones. A CM will encourage a participant to set reminders on his or her phone to assist with keeping appointments or taking medications. Unless a participant opts out, his or her CM will arrange for the delivery of both automated and personalized messages to help with the achievement of goals.[^68^](#_ENREF_68) From the focus groups, we learned releasees may want text messages to remind them of clinic appointments, to hold them accountable in challenging situations such as dealing with negative peer pressure, to serve as periodic check-ups for an update on status, and for general words of encouragement. Using the expertise of [name], we will design these messages tailored to a participant’s stated needs and literacy level. For example, illiterate participants may receive text-to-phone audio messages. The study team will initiate message once per week for the 60 days of the post release period. **Session 4** will focus further on linkage to services that can reduce risk in problematic areas, such as treatment for substance abuse that hinders medication adherence or mental health treatment that might interfere with maintaining employment. With the help of his or her CM, a participant will map out the steps needed to gain entry into treatment programs. At **Session 5,** a participant and his or her CM will review progress on how well the contact plan was achieved. **Session 6** will focus on disengagement and transition to the clinic’s usual case management. The typical participant will receive 6 sessions, all of which should be completed within the first 60 days post-release. Missed sessions can be rescheduled, as soon as is possible. After the 6 initial sessions, a participant may informally contact his or her CM by phone or in person for review of the contact plan, but if more intense case management is needed, the study CM will make a referral to case management through a participant’s medical home. Although sessions 1 and 2 are designed to be delivered in jail and sessions 3 through 6 in the community, the program includes the necessary flexibility so that most sessions could be delivered in or out of the jail setting. This is necessary given the unpredictability of jail release dates and the potential for re-incarceration. Text messaging and phone calls to a CM will occur throughout the period of SBCM delivery.

2. Describe total respondent burden: the baseline demographic data will take less than 30 minutes to complete. The intervention will involve 6-20 hours of face time with a case manager.

**e. Measures**

***Process measurement*:** we will determine if 42 participants can be enrolled in three months and that SBCM can be delivered according to the SUCCESS intervention protocol. [name], assisted by [name], will oversee evaluation of the CMs. We anticipate the 2 CMs will each be assigned 6-8 new clients a month (a total of 14 assigned per month); clients will stay in the “active phase” for 2 months after discharge. At bi-weekly meetings, [name] will determine if there is balance between the caseloads. [name] will review data on: (1) the number of intervention sessions that each client receives, and (2) any make-up sessions if initial visits are missed. We will monitor fidelity to the intervention protocol. With permission of the client, [name] will periodically observe sessions and afterwards discuss her observations with the CMs. CMs will document each contact with clients on their caseload, recording specific information about a session including: date, location and length of contact, presence of other persons or not, client use of cell phones, referrals to clinical and social services that are followed through and intensity of referral (e.g., phone call only or went with client to referral). Further, CMs document what barriers to linking with medical care were discussed during each session.

[name] will oversee the conduction of independent observation of staff-client interactions. The basis for these observations will be the ARTAS-like Case Management Fidelity Scale consisting of five areas that are central to the delivery of strengths-based interventions such as SUCCESS. These areas include: focus on strengths, encouragement of client-driven activities, relationship building, assertive outreach, and use of resources. She will rate CMs on 29 specific tasks in the five areas using a 5 point Likert-like scale that asks whether she Disagree Strongly (1) to Agree Strongly (5) that a CM has delivered a task with full fidelity. Using a random number generator to select sessions, we will audiotape a random sample of 10% of sessions in the community (and in the jail when policy permits audiotaping—jail policy can change with time). [name] and Project Coordinator [name], assisted by [name], will monitor the conduction of the intervention activities by reviewing the audio-taped sessions on a weekly basis. [name] will provide feedback to CMs based on their scores on the fidelity scale. Prompt discussion of fidelity scores has been demonstrated to be an effective tool in improving adherence to intervention protocols. Additionally, the CMs will present cases at bi-weekly supervisory sessions. These sessions will allow [name] the opportunity to monitor adherence to SUCCESS, provide a teaching opportunity in areas she feels need additional attention, address and resolve any problems that may arise during the intervention, and ensure fidelity to the protocol.

***Outcomes measurement:*** The primary outcome will be whether a participant linked to community HIV care and, if it occurs, how long before a linkage occurred, with the clock starting at the initial release from jail. Linkage to care will be defined as a visit to an HIV provider that entails the acquisition of an HIV viral load and CD4 cell count. This outcome will be assessed at 3 months and will be measured in days between initial jail discharge and laboratory draw. This measurement will be adjusted for the number of days at liberty, since participants may return to jail one or more times in those 3 months post initial release. The interval of 3 months post initial release, rather than a shorter period, is warranted because participants who had a medical visit within a month prior to incarceration and, upon release, returned to the clinic within 3 months of their last visit, would still be considered linked to care by national performance guidelines[^69^](#_ENREF_69) **Chart review.** The study team will review the jail medical records and the community HIV medical clinic records at 3 months in order to gather data on whether a face to face visit occurred with a provider and whether laboratory tests (CD4 and HIV RNA) were ordered.

1. **Risks to Participation**

Potential discomfort or risk to a subject includes 1) psychological distress if a participant feels coerced to participate, and 2) breach of confidentiality of health information. This research does not adversely affect a participant’s rights and welfare, provided that the confidentiality of identifying information is maintained. The two potential risks listed above will be addressed in the following manner:

1. Subjects may experience psychological stress if they feel coerced to participate. However, the likelihood of this risk is small. When the study team solicits informed consent, potential participants will be told that their enrollment is voluntary. Furthermore, enrolling in the study will not affect the conditions of any parole or probation. Participant incentives in this study are nominal and will be given to participants only after reentry to the community. Participants may separate from the study at any point without any penalty.
2. To minimize the risk of a breach of confidentiality of any medical data (including HIV status and other sensitive information), participants will be assigned study ID numbers. These numbers, rather than personally-identifiable information, will be associated with data. Confidential information, including health information, will be stored in a locked drawer in a locked study office. Only study staff will have access to the keys. The audio recordings of the focus group will be destroyed at the completion of the study. Standards for privacy of individually identifiable health information under the Health Insurance Portability and Accountability Act of 1996 will be met. HIPAA Authorization documentation will be incorporated into the consent forms that will be obtained from participants. The only information that will not be kept confidential is if volunteers or members of the study staff believe that program participants are a danger to themselves or others; or if minor children are under control of the participant, and there is reasonable evidence that the children are at risk.
3. **Benefits to Subject**

The findings of this study will help inform future adaptations of the intervention to jails in urban settings. These future adaptations could help inform policy makers of structural interventions to improve linkage to care for HIV-positive jail releasees. Population subgroups disproportionately affected by incarceration will be the greatest beneficiaries. In addition to receiving a small cash incentive, individual study participants may benefit from improved linkage to care, as facilitated by the SBCM intervention sessions.

1. **Data Analysis**

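### The 10% fidelity tapes are drawn without stratification, so they will probably be spread unevenly over session types and case managers; stratifying the same 10% is a minor, low-cost improvement

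*Protocol*

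**What the plan says.** Protocol section 2.e (Measures, process measurement) makes delivery a feasibility question: "we will determine if 42 participants can be enrolled in three months and that SBCM can be delivered according to the SUCCESS intervention protocol". The tapes are one source of evidence on it. The selection rule is "Using a random number generator to select sessions, we will audiotape a random sample of 10% of sessions in the community", extended by "and in the jail when policy permits audiotaping". The section names no stratum, no number of tapes, and no rule for a selected session that does not take place.

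The rater scores case managers on 29 tasks in five areas, and the scores are the basis for feedback to them. The same section also plans periodic live observation with the client's permission, case-manager notes on every contact, and supervisory meetings every two weeks at which cases are presented.

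Section 2.d (Study Procedures) gives the six sessions different content: contact plan and benefits forms, rapport and strengths assessment, release and clinic contact, linkage to treatment services, review of progress, and disengagement. It says "The typical participant will receive 6 sessions" and that "sessions 1 and 2 are designed to be delivered in jail and sessions 3 through 6 in the community", with flexibility in both directions.

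The number of case managers differs between sections. In 2.d the intervention "will be delivered by the study’s three CMs". In 2.e the text reads "We anticipate the 2 CMs will each be assigned 6-8 new clients a month (a total of 14 assigned per month".

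**The concern.** The taped sample is small and is spread over sessions that differ in purpose and over two or three case managers. An unstratified draw leaves that spread to chance. If a session type has no tape or only one, the tapes say little about whether that part of the intervention was delivered as designed. If one manager's tapes come mostly from one kind of session, that manager's score may partly reflect the mix of sessions, because not every session is likely to give equal occasion for tasks such as assertive outreach or relationship building. Missed later sessions would thin the sample further at the end of the programme. A session that was not taped cannot be recovered afterwards.

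**Working it through.** **Inputs.** 14 per month × 3 months = 42 participants, the protocol's own figure. Six sessions each, planned as 1–2 in jail and 3–6 in the community. Taping fraction 10%. Two case managers (2.e) or three (2.d). Equal caseloads are assumed.

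**Number of tapes.**
- All sessions delivered and tapeable: 42 × 6 = 252; 10% is 25.2, taken as 25.
- Sessions 3–6 only: 42 × 4 = 168; 10% is 16.8, taken as 17.

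**Method.** For m tapes drawn without replacement from N sessions, the chance that a given group of c sessions has no tape is C(N−c, m)/C(N, m). The chance that at least one group is empty, or has at most one tape, follows by exact counting over all groups.

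**Coverage of a single factor, 25 of 252 unless stated.**
- A whole case manager untaped: 2 × C(126,25)/C(252,25) = 1.6 × 10⁻⁸ with two managers; about 6 × 10⁻⁵ with three. With 17 of 168 tapes and three managers it is at most 3 × C(112,17)/C(168,17) = 0.2%.
- A given session number untaped: C(210,25)/C(252,25) = 0.8%. At least one of the six: 4.8%. For sessions 3–6 only (17 of 168): 2.2%.
- At least one session number with no more than one tape: 30%. For sessions 3–6 only: 17%.

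**Assumed attrition.** The protocol gives no rate of missed sessions. If 10% of clients are lost at each step, the six session numbers have about 42, 38, 34, 31, 28 and 25 sessions, 198 in all, giving 20 tapes. Then some session number has at most one tape in about 64% of draws and none in about 16%.

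**Case manager by session number, full delivery.**

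| Tapeable sessions | Managers | Cells × sessions per cell | Tapes | Given cell empty | Mean empty cells | At least one empty |
|---|---|---|---|---|---|---|
| 252 | 2 | 12 × 21 | 25 | 10.1% | 1.2 | 77.6% |
| 252 | 3 | 18 × 14 | 25 | 22.2% | 4.0 | 99.8% |
| 168 | 2 | 8 × 21 | 17 | 9.1% | 0.7 | 58.4% |
| 168 | 3 | 12 × 14 | 17 | 21.1% | 2.5 | 98.0% |

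The results do not depend on exact assumptions. With all sessions tapeable and two managers, selecting each session independently with probability 10% gives 75.1%, and an 18/24 split of clients gives 79.6%. The 10% loss per step with two managers gives 94%.

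**Same tapes, stratified.** 25 tapes cover 12 cells twice (24, plus 1 spare) or 18 cells once (18, plus 7). 17 tapes cover 8 cells twice (16, plus 1) or 12 cells once (12, plus 5). No tapeable cell is then empty at full delivery. Without stratification, bringing the risk of an empty cell below 5% on the 252-session basis would take about 56 tapes (22%) for 12 cells or 85 (34%) for 18.

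**The case against.** The strongest reply is that the protocol never asks for every combination of manager and session number to be taped. The scale rates managers on tasks that are not tied to a session number, and no analysis by cell is planned, so the 58% to 99.8% figures measure a standard that the protocol did not set. This stands, and it is why the point is not an error. A random 10% also represents the delivered sessions without bias; stratifying improves balance but does not correct a bias.

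A reader might infer that some case managers will go unassessed. The figures rule that out: a manager with no tape at all has a chance of 0.2% or less. A reader might also infer that some session content will never be heard. Session numbers are usually taped at full delivery, and live observation, contact notes and case presentations also monitor delivery. The frequency and selection of the live observations are not stated, so they do not guarantee coverage, but they do mean that untaped is not the same as unmonitored.

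Finally, this is a one-arm pilot of 42 that says it will not rigorously test its tools or the intervention, and nothing here touches enrolment or linkage. That limits the weight of the point. It does not remove it, since delivery according to protocol is a stated process measure and the sampling rule is one that the protocol itself fixes.

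**Conclusion.** The point holds as a minor improvement. At full delivery with all sessions tapeable, the unstratified 10% leaves a 30% chance that some session number has at most one tape. In each full-delivery scenario in the table, an untaped combination of manager and session number is more likely than not. Coverage of each manager is secure, and complete loss of a session number is uncommon (about 5%, or about 16% under the assumed attrition).

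These figures rest on reading the sampling rule as an unstratified draw, which is its plain sense though the text says only that the sample is random. They also rest on equal caseloads and, outside the attrition case, on all six sessions being delivered. The count of 25 tapes further needs jail taping to be permitted.

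**What to change.** 1. Reconcile the two case managers in section 2.e with the three in section 2.d, since this sets the number of strata.
2. Keep the 10% fraction, but draw it within strata of session number by case manager among tapeable sessions: at least one tape per cell where the number of tapes allows, otherwise balanced by session number. The fallback is needed: with community taping only and an assumed 30% loss per step, 52 sessions give about 5 tapes for 8 cells.
3. If a selected session does not take place, tape the next session in the same stratum.
4. Report fidelity by session number and by manager. If an overall score is given, say whether session types are weighted equally or by number delivered.

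**Cost.** The same fraction is taped and reviewed. The list needs light prospective tracking by manager and session number, which the existing contact notes and session counts can largely supply, and it must be in place before sessions begin. Jail sessions stay untaped under any scheme while policy bars recording; the report should say so.
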